## 5.3 Study procedures

### 5.3.1 Setting up the research team

There will be 17 research teams, one for each study site. The research team will consist of two nurses, one general practitioner and one pediatrician. There will be a central technical team composed of pediatricians, neonatologists, child health program experts and research experts. One pediatrician in each study hospital will be ensured and responsible for the monitoring of study activities.

**Fig.4. Structure and responsibility of the research team**

[figure not shown]

### **5.3.3**

#### **5.3.4 Training**

For the feasibility & effectiveness study a two days training will be given to two nurses, one general practitioner and one pediatrician per facility. The training will be on how to explain the information sheet and get informed consent from parents/caregivers of study participants. They will also be trained on the data collection tools and preparation of locally constructed bubble CPAP. The trainers will be from the central technical team.

For the acceptability study a one day training will be given to qualitative data collectors on facilitating focused group discussion and conducting in depth interviews.

## **6. Ethical consideration**

The study protocol will be submitted to Tikur Anbessa Specialized Hospital, St. Pauls' Millennium Medical College, AHRI Institutional Ethical Review Board and National Ethics Review Board of Ethiopia and icddr, b IRB for ethical approval. Written informed consent will be obtained from parent or guardian of each study participants.

All data from the study participants will be kept in a locked cabinet at AHRI and will only be accessed by the study investigators. During publication, all patient identifiers will be removed in order to keep confidentiality.

Data Safety monitoring board (DSMB) will be established which will consist of one Pediatrician, one statistician, one Epidemiologist and Pediatric Intensivist who have knowledge on bubble CPAP. Results will be reported to the DSMB every 3 months and interim analysis will be done at 6 months of Stage III trial after which actions will be taken accordingly. All severe adverse events and deaths will be communicated to the DSMB within 24 hours.

## **7. Project Risks and Risk-Management strategies**

This study does not introduce major risks to participants beyond what they would normally face in their condition. As it will be an interventional study with bubble CPAP oxygen therapy, side effects such as nasal trauma, nasal obstruction, gastric distension and pneumothorax are occasionally reported while using bubble CPAP in neonates but such complications are extremely rare in older children. In order to minimize those risks, all the necessary precautions will be taken with routine follow ups. We shall not perform any laboratory investigations for the study purpose except those required for routine care as determined by the hospital clinicians. Breaching medical confidentiality is also a risk. Training and standard SOPs will be implemented to help avoid these problems.

If a significant event caused as a direct result of participation in the study, the study staff will document the incident, inform the site PI, and local medical costs incurred, will be covered by the study's local medical malpractice insurance that is provided by the study.

## **8. Declaration of potential conflicts of interests**

We declare no competing interests.

## **9. Recording and reporting of adverse and serious adverse events:**

Following standard operating procedure, the study staff will document all incidents of adverse events and serious adverse events that are associated with participation in the study, inform the site PI, and local medical costs incurred will be covered by the study's local medical malpractice insurance that is provided by the study. Any serious adverse event (whether it is related to the intervention or not) and the actions taken will be reported to FMHACA within 48 hours of occurrence. In addition, summary of adverse events will be reported to FMHACA quarterly.

Indemnification and insurance:

The insurance policy will include both classical clinical trial insurance and indemnification insurance. A local insurance company will be responsible for them. The title of the trial, amount of insurance in respect of each participant, the number and/ or name of health facilities involved in the study are indicated in the insurance certificate.

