|                                                   |                                                                                                                                                                                                                                                                                                                                                                                                                                                                                                                                                                                                                                              |
|---------------------------------------------------|----------------------------------------------------------------------------------------------------------------------------------------------------------------------------------------------------------------------------------------------------------------------------------------------------------------------------------------------------------------------------------------------------------------------------------------------------------------------------------------------------------------------------------------------------------------------------------------------------------------------------------------------|
|                                                   | 
-Continuous variables will be analyzed using the Student t-test or the Mann-Whitney test as appropriate.
 
-The primary outcome of the study is treatment failure and the secondary outcomes are death, pneumothorax, abdominal distention, nasal trauma, aspiration pneumonia.
 
-Primary and secondary outcomes will be compared by calculating relative risks (RRs) and their 95% confidence intervals.
 
- Log-linear binomial regression will be applied to adjust for covariates to evaluate the true impact of bubble CPAP in evaluating primary and secondary outcomes and to adjust for baseline differences.
 |

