## Secondary Outcomes

- Death during hospitalization
- Deaths during hospitalization plus within 72 hours of LAMA
- Pneumothorax
- Aspiration pneumonia
- Length of hospital stay
- Incidence of nasal trauma, gastric distention, shock and air leaks
- Duration of bCPAP

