## Sample and sampling procedure:

In this trial, our recruitment goals are approximately a total of 1240 children (620 children each for LF oxygen and bubble CPAP therapy) for a power of 80% and effect size of 50% (reduction of treatment failure, primary outcome of the study, from chart analysis 10% treatment failure in 2019 in comparison facilities) for 12 clusters (103-104 patients in each cluster), adjusted for a intra-cluster correlation coefficient (ICC) level of 0.003 required for cluster randomization. For the calculation of sample size we have used following formula:

Where,  $DF$ , Design effect =  $1 + \delta(m-1)$  [here  $DF=1.52$ ],

$n_1$  = Required minimum sample size per arm,  $\delta$  = the inter cluster correlation,  $m$  = the number of patients in each cluster [103.3 in this study],

$P_1$  = the percentage of treatment failure of children with pneumonia receiving standard treatment (low flow) = 10%,

$P_2$  = the expected percentage of treatment failure of children with pneumonia who will receive intervention (bubble CPAP) = 5% [we have observed 5% treatment failure in two district hospitals during the stage II of our study which correspond 50% effect size],  $Z_\alpha$  = the z-score value [here,  $Z_\alpha = 1.96$  at 5% level of significance],  $Z_\beta$  = the z-score value [here,  $Z_\beta = 0.84$  at 80% power]. We are intending to enroll same number of children (103-104) having our eligibility criteria from each hospital (cluster) irrespective of receiving intervention (bubble CPAP) or standard treatment (low flow).

As a run-in period we will enroll 2 participants in each hospital which will be excluded from final analysis.

**Data collection:** Data will be collected by individual patient assessment through systematic observations using a structured questionnaire. Socio-demographic and different clinical data will be collected. The questionnaire will include the baseline characteristics, intervention and outcome data. All study data will be collected by dedicated study personal at sites.

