### 3. Monthly income

a. <500br

b. 500-1000 br

c. 1000-2000br

d. >2000br

e. house hold assets

1. Sex: Male ☐ Female ☐ Age (yrs): \_\_\_\_\_ Weight (kg): \_\_\_\_\_  
Height (cm): \_

2. History of presenting illness: Cough -----

Fever -----

Fast breathing/SOB-----

Others specify-----

3. Duration of illness in days-----

4. New-----Repeated----- date of last admission-----

5. Clinical findings

| Parameter          | Admission | 1 hour | 6 hours | 12 hours | 24 hours | 48 hours | 72 hours |
|--------------------|-----------|--------|---------|----------|----------|----------|----------|
| Respiratory rate   |           |        |         |          |          |          |          |
| Nasal flaring      |           |        |         |          |          |          |          |
| Chest indrawing    |           |        |         |          |          |          |          |
| Grunting           |           |        |         |          |          |          |          |
| Cyanosis           |           |        |         |          |          |          |          |
| Consciousness(GCS) |           |        |         |          |          |          |          |
| Oxygen saturation  |           |        |         |          |          |          |          |
| Temperature        |           |        |         |          |          |          |          |

|            |  |  |  |  |  |  |  |
|------------|--|--|--|--|--|--|--|
| Heart rate |  |  |  |  |  |  |  |
|            |  |  |  |  |  |  |  |
|            |  |  |  |  |  |  |  |

5. CXR finding-----

6. HIV status

- a. Negative
- b. Positive
- c. Exposed
- d. Unknown

8. Type of antibiotic started -----

9. Length of hospital stays in days -----

10. Length of stay on bubble CPAP in days-----

11. Outcome of the patient?

- a. Intubated and put on mechanical ventilation
- b. Improved and discharged
- c. Died
- d. Discharged against medical advice

12. Any complications noted

- a. Nasal trauma      yes      No
- b. Nasal obstruction yes      No
- c. Gastric distension yes      No
- d. Pneumothorax      yes      No

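### Section 9 limits adverse-event recording to events associated with participation, and aspiration pneumonia, shock and other air leaks, which are comparative secondary outcomes, have no field on the case form to offset this

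*Protocol*

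**What the plan says.** Protocol section 9 opens with the recording rule: "the study staff will document all incidents of adverse events and serious adverse events that are associated with participation in the study". The same sentence goes on to informing the site investigator and to insurance cover of medical costs. The next sentence sets a different condition for serious events: "Any serious adverse event (whether it is related to the intervention or not) and the actions taken will be reported to FMHACA". Section 6 has a third rule, also without an attribution condition: "All severe adverse events and deaths will be communicated to the DSMB within 24 hours".

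Several adverse events are efficacy-style endpoints as well as safety reports. The Stage III secondary outcomes in section 5.2 include pneumothorax, aspiration pneumonia and "Incidence of nasal trauma, gastric distention, shock and air leaks". The Summary says that "the secondary outcomes are death, pneumothorax, abdominal distention, nasal trauma, aspiration pneumonia". Both the Summary and the Stage III data analysis paragraph plan relative risks with 95% confidence intervals for the secondary outcomes.

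Outcome data are to come from a form. Section 5.2 states that "Data will be collected by individual patient assessment through systematic observations using a structured questionnaire" and that "The questionnaire will include the baseline characteristics, intervention and outcome data". On that form (Annex 9), item 12, headed "Any complications noted", has yes/no answers for nasal trauma, nasal obstruction, gastric distension and pneumothorax. It has no relatedness question, no limit to one arm and no line for other events.

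**The concern.** An event that serves as a between-arm outcome has to be ascertained by the same rule in both arms, and suspected cause should play no part in whether it is recorded. A rule that admits an event only if it is associated with taking part works differently by arm when staff know the allocation. In one set of hospitals taking part means a new device. In the other it means the usual low-flow oxygen. Staff may link the same event to the study more readily in the first setting than in the second.

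The recorded counts could then differ between arms even if the true risks were equal, and the relative risk would carry that difference. The trial is meant to inform wider use of the device, so its safety comparison matters. Events not recorded at the time may not be recoverable later.

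**Working it through.** **1. The rules for serious and severe events, side by side**

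| Place | Events covered | Attribution condition |
|---|---|---|
| Section 9, first sentence | adverse and serious adverse events, documented | yes, association with participation |
| Section 9, next sentence | any serious adverse event, reported to the regulator | none |
| Section 6 | severe adverse events and deaths, sent to the monitoring board | none |

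A serious event cannot be reported regardless of relatedness if it is documented only when associated with the study. The first row conflicts with the other two.

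**2. Which secondary outcomes the case form protects**

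| Stage III secondary outcome | Own field in Annex 9 item 12 |
|---|---|
| Pneumothorax | yes |
| Nasal trauma | yes |
| Gastric distension | yes |
| Aspiration pneumonia | no |
| Shock | no |
| Air leaks | only pneumothorax |

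The rest of Annex 9 does not fill the gap. The outcome item offers ventilated, improved and discharged, died, or discharged against advice. The table of clinical findings names heart rate and consciousness but no blood pressure or perfusion row. The chest X-ray entry is one undated free-text line. For non-serious aspiration pneumonia, shock and other air leaks, the first sentence of section 9 is therefore the only recording rule shown.

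**3. What unequal recording does to a relative risk**

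The protocol gives no adverse-event rate or capture rate, so there is no stated figure to reproduce. Let p1 and p0 be the true risks on bubble CPAP and low-flow oxygen, and c1 and c0 the proportions of true events that are recorded. Ignoring false entries:

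observed RR = (p1 × c1) / (p0 × c0) = true RR × (c1 / c0)

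With a true RR of 1 and **assumed** capture rates:

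| c1 | c0 | Observed RR |
|---|---|---|
| 100% | 90% | 1.00/0.90 = 1.11 |
| 90% | 70% | 0.90/0.70 = 1.29 |
| 100% | 70% | 1.00/0.70 = 1.43 |
| 90% | 50% | 0.90/0.50 = 1.80 |
| 100% | 50% | 1.00/0.50 = 2.00 |
| equal | equal | 1.00 |

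**4. The same in counts**

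Take the planned 620 children per arm, an assumed true risk of 4% in both arms, and assumed capture of 90% and 50%:

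- bubble CPAP: 620 × 0.04 × 0.90 = 22.3 recorded events
- low-flow oxygen: 620 × 0.04 × 0.50 = 12.4 recorded events
- observed RR = 22.3/12.4 = 1.80
- SE(log RR) = √(1/22.3 + 1/12.4 − 2/620) = 0.35
- 95% CI = exp(log 1.80 ± 1.96 × 0.35), about 0.91 to 3.57, with clustering ignored

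Even this large assumed imbalance gives an interval that includes 1. Allowing for clustering would widen it.

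**The case against.** A reader might infer that every adverse event is documented only after being judged related to the study, so that all the safety comparisons are distorted. The documents do not support that, for these reasons:

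- Annex 9 item 12 captures nasal trauma, gastric distension and pneumothorax with no attribution filter, and section 5.2 describes systematic assessment of each patient.
- Serious events, severe events and deaths have unfiltered reporting routes. Some cases of shock or aspiration pneumonia would probably travel by them.
- No causality assessment or assessor is described, so the word judged would go beyond the text. The protocol also does not call the trial open-label. That is inferred from the devices and from the absence of any blinding.
- The sentence in section 9 is tied to insurance cover and refers to an operating procedure that is not shown. Association with participation could mean no more than occurrence during it.
- Missing tick-boxes affect both arms alike. They bias a relative risk only if recording then differs by arm.
- All capture rates and the 4% risk above are assumptions.

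Most of this stands, and it narrows the point to three outcomes. Two parts do not remove it. The unfiltered routes are expedited reporting channels, and nothing says that they feed the outcome dataset or that they reach non-serious events. The benign reading of association is also weakened by section 7, where a closely similar clause on documentation and cost cover applies to events that result directly from taking part. A causal reading of section 9 is therefore at least as natural. If the other meaning was intended, the text should say so.

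**Conclusion.** The point holds in a limited form. Section 9 contradicts itself and section 6 on serious events. For non-serious aspiration pneumonia, shock and air leaks other than pneumothorax, the only recording rule shown depends on an undefined association with participation. Counts of these outcomes may be incomplete or may depend on the arm, and their relative risks may be biased by the ratio of the two capture rates.

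The size cannot be derived from the protocol. The illustrated values of 1.11 to 2.00 rest wholly on assumed capture rates, and on the assumption that recording is more complete in the bubble CPAP hospitals. If capture is equal there is no bias, only fewer events. The documents do not support a claim that bias will occur, or that the planned safety comparisons as a whole cannot be interpreted. The primary outcome and the three events with their own fields are not affected.

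**What to change.** 1. In section 9, delete the clause that restricts documentation to events associated with participation. State that all adverse and serious adverse events are recorded in both arms regardless of suspected cause.
2. Record relatedness as a separate field, so that it can serve regulatory reporting without deciding whether an event enters the data.
3. Add yes/no items for aspiration pneumonia, shock and air leaks to Annex 9 item 12, to be completed for every child in both arms.
4. Check that the first two sentences of section 9 and the reporting rule in section 6 then agree.

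The cost is one sentence, one field and three tick-boxes, with slightly more recording at the sites. The sample size and the planned analysis do not change.

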## **Protocol deviation**

In case of protocol deviations, a deviation form will be filled out by study staff and sent to the DSMB within 72 hours of the events.

## **10. Amendment of the protocol**

If we need any amendment of the protocol during the study period we will provide amendment request to IRBs at AHRI, NREREC, and icddr,b.

11. Termination of the trial will be decided by the data safety monitoring board after analyzing quarterly report of the trial, and before termination the study sponsor and PI will inform IRBs at AHRI, NREREC, and icddr,b and FMHACA.

## **12. Final reporting, dissemination and publication**

After the end of the study the results will be reported nationally and internationally by attending national and international scientific conferences and by arranging dissemination programs in Ethiopia, Bangladesh and other developing countries. Additionally we will publish the findings in international peer reviewed journal(s). Both AHRI and icddr,b will be the owner of the collected data. However, all investigators will have access to the data and those fulfilling international authorship criteria will be included as authors in manuscripts reporting the study results. For the main manuscript, the study PIs (Drs [name] and [name]) of this study will be the co-first authors of the main manuscript. One investigator from the Ethiopia and one from icddr,b (Professor [name]) will be the co-senior authors of this manuscript written from this study. If there will be more than one manuscript from this study, first authorship will be discussed and allocated according to international standards of authorship before preparing the draft.

## **Roles of icddr,b, AHRI, and FMOH**

### **a. Roles of icddr,b:**

- i) Conceptualize and design of the study in collaboration with AHRI
- ii) Attaining the funding for the study from SIDA Sweden for the collaboration
- iii) Assist in procuring equipment for the study following signed memorandum of understanding between icddr,b and AHRI.
- iv) Externally supervise & monitor the study following SOP
- v) Provide training for staff development following SOP
- vi) Provide technical and logistical support to the study, including on-site support following signed memorandum of understanding between icddr,b and AHRI.
- vii) Assist in developing data management system for data entry, cleaning, analysis and reporting of the research findings following SOP.
- viii) Help local PI to organize training for study personnel from each research site following SOP

### **b. Roles of AHRI:**

- i) Conceptualization and design of the study in collaboration with icddr,b
- ii) Attaining the funding for the study from DFID Ethiopia for the collaboration
- iii) Recruit and train staff

- iv) Supervise and monitor the study
- v) Assist in procuring necessary supplies for the study
- vi) Make the necessary payments for the study personnel
- vii) Development of data management system in collaboration with icddr,b for data entry, cleaning, analysis and reporting of the research findings following SOP
- viii) Organize training for study personnel from each research site

### c) Roles of FMOH

- i) Provide support letter to study sites for the conduct of the study
- ii) Follow the general progress of the research project

## 12. Work Plan

| Activities                                                                      | 1 | 2 | 3 | 4 | 5 | 6 | 7 | 8 | 9 | 10 | 11 | 12 | 13 | 14 | 15 | 16 | 17 | 18 | 19 | 20 | 21 | 22 | 23 | 24 | 25 | 26 | 27 | 28 |
|---------------------------------------------------------------------------------|---|---|---|---|---|---|---|---|---|----|----|----|----|----|----|----|----|----|----|----|----|----|----|----|----|----|----|----|
| Development of protocol                                                         |   |   |   |   |   |   |   |   |   |    |    |    |    |    |    |    |    |    |    |    |    |    |    |    |    |    |    |    |
| Clearances at icddr,b and AHRI                                                  |   |   |   |   |   |   |   |   |   |    |    |    |    |    |    |    |    |    |    |    |    |    |    |    |    |    |    |    |
| Training of trainers at icddr,b                                                 |   |   |   |   |   |   |   |   |   |    |    |    |    |    |    |    |    |    |    |    |    |    |    |    |    |    |    |    |
| Selection, randomization, and training of clinical sites: care, data collection |   |   |   |   |   |   |   |   |   |    |    |    |    |    |    |    |    |    |    |    |    |    |    |    |    |    |    |    |
| Trial in two tertiary hospitals (Stage I)                                       |   |   |   |   |   |   |   |   |   |    |    |    |    |    |    |    |    |    |    |    |    |    |    |    |    |    |    |    |
| Trial in two rural district hospitals (Stage II)                                |   |   |   |   |   |   |   |   |   |    |    |    |    |    |    |    |    |    |    |    |    |    |    |    |    |    |    |    |
| Implementation Stage: main trial (Stage III)                                    |   |   |   |   |   |   |   |   |   |    |    |    |    |    |    |    |    |    |    |    |    |    |    |    |    |    |    |    |
| Final cleaning and freezing of data set                                         |   |   |   |   |   |   |   |   |   |    |    |    |    |    |    |    |    |    |    |    |    |    |    |    |    |    |    |    |
| Analysis and report writing                                                     |   |   |   |   |   |   |   |   |   |    |    |    |    |    |    |    |    |    |    |    |    |    |    |    |    |    |    |    |
| Dissemination, policymaker discussions                                          |   |   |   |   |   |   |   |   |   |    |    |    |    |    |    |    |    |    |    |    |    |    |    |    |    |    |    |    |

